## Abstract

**Background:**

Reducing youth suicide in the United States (U.S.) is a national public health priority, and lesbian, gay, bisexual, transgender, and queer or questioning (LGBTQ) youth are at elevated risk. The Centers for Disease Control and Prevention (CDC) endorses six evidence-based (EB) strategies that center on meeting the needs of LGBTQ youth in schools; however, fewer than 6 % of U.S. schools implement all of them. The proposed intervention model, “RLAS” (Implementing School Nursing Strategies to Reduce LGBTQ Adolescent Suicide), builds on the Exploration, Preparation, Implementation, and Sustainment (EPIS) conceptual framework and the Dynamic Adaptation Process (DAP) to implement EB strategies in U.S. high schools. The DAP accounts for the multilevel context of school settings and uses Implementation Resource Teams (IRTs) to facilitate appropriate expertise, advise on acceptable adaptations, and provide data feedback to make schools implementation ready and prepared to sustain changes.

**Methods/Design:**

Mixed methods will be used to examine individual, school, and community factors influencing both implementation process and youth outcomes. A cluster randomized controlled trial will assess whether LGBTQ students and their peers in RLAS intervention schools (*n* = 20) report reductions in suicidality, depression, substance use, bullying, and truancy related to safety concerns compared to those in usual care schools (*n* = 20). Implementation progress and fidelity for each EB strategy in RLAS intervention schools will be examined using a modified version of the *Stages of Implementation Completion *checklist. During the implementation and sustainment phases, annual focus groups will be conducted with the 20 IRTs to document their experiences identifying and advancing adaptation supports to facilitate use of EB strategies and their perceptions of the DAP.

**Discussion:**

The DAP represents a data-informed, collaborative, multiple stakeholder approach to progress from exploration to sustainment and obtain fidelity during the implementation of EB strategies in school settings. This study is designed to address the real-world implications of enabling the use of EB strategies by school nurses with the goal of decreasing suicide and youth risk behaviors among LGBTQ youth. Through its participatory processes to refine and sustain EB strategies in high schools, the RLAS represents a novel contribution to implementation science.

**Trial registration:**

ClinicalTrials.gov, NCT02875535

**Electronic supplementary material:**

The online version of this article (doi:10.1186/s13012-016-0507-2) contains supplementary material, which is available to authorized users.

## Background

In 2012, the United States (U.S.) Surgeon General identified lesbian, gay, bisexual, transgender, and queer or questioning (LGBTQ) youth as at heightened risk for suicide [1]. Risk factors include depression, substance use, inadequate social support, and not feeling safe at school [1–7]. Large population-based studies over the past 15 years have found that lesbian, gay, and bisexual (LGB) youth are at two to four times increased risk for suicidal ideation and attempts when compared to their cisgender, heterosexual peers [1–3, 5, 8–16]. Within LGB populations, suicidality disproportionately affects racial and ethnic minorities, including American Indian and Hispanic people [1, 17, 18]. In numerous surveys and qualitative studies, transgender youth report elevated risk for suicide, depression, and substance use [19–24].

In general, LGBTQ youth report high levels of rejection, harassment, victimization, violence, and sexual abuse that can contribute to mental health problems and suicide behaviors [3, 9, 13, 18, 25]. These behaviors relate to “minority stress,” i.e., chronic stress from stigmatization, prejudice, and discrimination [26]. National school climate surveys have found that LGBTQ youth are often exposed to minority stress in schools [25, 27]. Youth describe being victimized because of their known, or perceived, sexual orientation or gender identity [8–11, 13, 19, 27]. LGBTQ youth are also more likely to experience high school victimization when they disclose their orientation, self-identify as a sexual minority, recognize same-sex feelings at a younger age, or demonstrate gender-atypical behavior [14, 28].

LGBTQ youth with greater school connectedness and safety report lower suicidal ideation and attempts [29]. Gay-Straight Alliances (GSAs)—peer-to-peer support groups—protect against suicide and depression for LGBTQ students [25, 30–34]. School policies are also pivotal to the mental health of LGBTQ youth. LGBTQ students at schools with anti-harassment policies may feel safer and are less likely to be harassed [35]. Those at schools with supportive staff, anti-bullying policies, and GSA clubs are less likely to be victimized, skip school because of safety concerns, or attempt suicide compared with those in other schools [32]. LGBTQ youth may be at lower risk for attempting suicide if they attend school in districts with anti-bullying policies covering sexual orientation and gender identity [36]. LGBTQ students in settings with more protective school climates report fewer suicidal thoughts than those in places with less protective climates [37].

A supportive, safe school environment is key to a comprehensive public health strategy to prevent youth suicide [38]. As a protective factor against suicidal ideation and attempts, school connectedness is second in importance only to family connectedness [39]. The Centers for Disease Control and Prevention (CDC) endorses six EB strategies for schools to meet the needs of LGBTQ youth (see Table 1) [40]. However, the 2012 School Health Profiles Report based on data from 44 states found that only 5.5 % of secondary schools implement all six [40].

**Table 1 Tab1:** Description of the school-based evidence-based strategies to meet the needs of LGBTQ youth

1. Identify “safe spaces” such as a counselor’s office, designated classroom, or student organization where LGBTQ youth can receive support from administrators, teachers, other school staff, or other students.
2. Prohibit harassment and bullying based on a student’s perceived or actual sexual orientation or gender expression.
3. Facilitate access to providers not on school property who have experience delivering health services, including human immunodeficiency virus (HIV)/sexually transmitted infection (STI) testing, counseling, and reproductive healthcare, to LGBTQ youth.
4. Facilitate access to providers not on school property who have experience in providing social and psychological services to LGBTQ youth.
5. Encourage staff members to attend professional development on safe and supportive school environments for all students, regardless of sexual orientation, gender identity, or gender expression.
6. Provide health education curricula or supplemental materials, i.e., HIV, STI, or pregnancy prevention information relevant, to LGBTQ youth (e.g., curricula or materials that use inclusive language or terminology).

Several factors within an organization can impact the success of implementation efforts. For example, organizational culture and climate influence staff willingness to engage in new practices [41], as do job tenure and level of professional development [42]. Leadership is also important [43]. Implementation leaders require capacity to be successful change agents and local champions, and their ability to motivate and interact effectively shapes staff attitudes toward adopting an EB strategy [44]. Personal innovativeness or ability to adapt or change can also impact attitudes toward new ways of working in a team or organization [45]. Provider attitudes toward adopting EB practices are also associated with actual utilization [46].

Schools are vital but largely untapped venues for intervention research on LGBTQ youth [2]. However, efforts to address the unmet mental health needs of youth in general and LGBTQ students specifically may not reach their full potential due to implementation challenges in school settings. The proposed intervention model, “RLAS” (Implementing School Nursing Strategies to Reduce LGBTQ Adolescent Suicide), builds on the Exploration, Preparation, Implementation, and Sustainment (EPIS) conceptual framework and the Dynamic Adaptation Process (DAP) to implement EB strategies in U.S. high schools [47, 48].

The EPIS framework segments implementation into four phases: *exploration* (considering new approaches to carry out EB strategies); *preparation* (planning to apply EB strategies); *implementation* (ongoing planning, training, coaching, and use of EB strategies); and *sustainment* (maintaining EB strategies over time) [47]. Per Fig. 1, the model emphasizes three levels of influence: system (or school), provider (or school nurse), and client (LGBTQ student). The model also attends to factors pertinent to both the “inner context” (e.g., schools, school nurses) and the larger “outer context” (e.g., policies, funding, resources) of EB strategy implementation and sustainment.

**Fig. 1 Fig1:**
[figure not shown]
Key Dynamic Adaptation Process components to support evidence-based strategy implementation per the Exploration, Preparation, Implementation, and Sustainment framework

The DAP is an implementation strategy guided by the EPIS framework that provides direction for activities to undertake during each EPIS phase and a continuously iterative data-informed approach to support EB strategy implementation [48]. The DAP has four key components: initial assessment; stakeholder engagement and training; problem solving; and outcomes feedback to address challenges. Another core feature of the DAP is the development of an Implementation Resource Team (IRT), a collaboration comprised of multiple stakeholders to assist with implementation, interpret data, and address adaptation as an explicit part of the implementation process.

Interventions to promote mental health in schools often fail because they want for leadership and staffing [49]. Leaders can positively or negatively impact the capacity to foster change and thus are instrumental in facilitating a positive climate and attitudes for implementing EB strategies [43, 44]. The Institute of Medicine has recommended that nurses in the U.S. should “practice to the full extent of their education and training” and be “full partners” in “redesigning healthcare” [50]. In the current study, school nursing expertise is applied in a distinctive way to lead IRTs in implementing the six EB strategies in their schools. This study combines qualitative methods (e.g., in-depth interviews and focus groups) with population-based surveys and other quantitative measures to pursue three specific aims:Utilize the DAP to enable specially-trained school nurse champions and IRTs to implement and sustain EB strategies to address the needs of LGBTQ high school students.Conduct a cluster randomized controlled trial to assess whether LGB youth and peers in RLAS intervention schools report reduced suicidality, depression, substance use, and bullying, and increased safety compared to control schools.Examine the individual, school, and community factors influencing implementation and outcomes.

## Methods/Design

### Study context

This work will occur in New Mexico (NM) high schools. Sociodemographic and minority stress factors contributing to adverse psychosocial outcomes are common in NM, which ranks 43rd in personal income per capita ($34,133) and second in persons below the poverty level (20.2 %) [51]. Of NM’s 33 counties, 32 are medically underserved [52]. Suicide rates for NM youth, ages 15 to 24, are nearly twice the national rate (19.7/100,000) [53, 54]. American Indian and Hispanic people comprise almost 56 % of 2,085,287 NM residents [55] and, like LGBTQ people, are disproportionately affected by health disparities [56, 57].

The New Mexico Youth Risk and Resiliency Survey (NM YRRS) is part of the nationwide CDC Youth Risk Behavior Surveillance System. The NM YRRS is administered to high school students in odd-numbered years and uses two discrete population-based sampling designs. A smaller sample provides data representative of the state and a larger sample furnishes data on specific populations not well represented in the smaller state sample. In 2013, data from 5451 students were obtained for the statewide sample and data from 19,080 students were obtained for the larger sample. A minority of students, 26.1 %, were White, non-Hispanic. Hispanics comprised 59.2 % of the population, African Americans, 0.9 %, and other races/ethnicities, 13.7 %. Half (48.8 %) of students were female [58]. Suicidality rates among NM students far exceeded national averages; 15.6 % seriously considered suicide, 13.7 % planned an attempt, and almost 1 in 10 (9.4 %) attempted it in the last year [59].

The 2013 NM YRRS was the first to include questions about same-sex sexual contact and sexual identity of NM high school students, which enables the NM Department of Health and schools to better understand the health and safety risks of students. Almost 11 % of the sample identified as LGB, with 3.0 % identifying as lesbian or gay and 7.5 % as bisexual [60]. In NM, LGB students experienced a relative lack of safety at schools: 35.5 % reported being bullied on school property in the last year, compared with 17.0 % of their straight peers; 17.3 % skipped school because of safety concerns, compared with 5.6 % of their peers [61]. Suicidality rates among NM LGB students were strikingly high with 38.3 % considering suicide, 35.4 % reporting making a suicide plan, and 28.5 % attempting suicide in the past year [61].

### Study design

This 5-year cluster randomized trial will include 40 NM high schools that employ a nurse on staff (*n* = 64). The schools will be randomized into the RLAS intervention condition (IC; *n* = 20) or the control condition (CC; *n* = 20). Cluster randomization was chosen because the intervention will be delivered at the school level. Schools will be eligible if they express interest in the full intervention and the school nurse and a lead administrator agree to participate and support the project. To minimize confounding effects, eligible schools will share the following characteristics: (1) public high school; (2) school nurse willingness to convene an IRT if randomized to the IC group; and (3) informed written consent from the school nurse to participate for four years. Additional file 1 contains confirmation of ethical approval.

From the IC schools, there will be three study populations: (1) school nurses; (2) school administrators; and (3) IRT members. From CC schools, there will be two study populations: (1) school nurses and (2) school administrators. School nurses and IRTs in the IC schools will receive innovation supports to encourage greater implementation of the six EB strategies (see Table 1). Nurses in the IC will recruit IRT members (4–6 people) willing to work with them on implementing the six EB strategies. These nurse champions will function as coordinators who keep the IRTs motivated, cohesive, and focused on goals; gain administrative buy-in during the Preparation Phase; and facilitate IRT planning in the Implementation Phase.

### Aim 1: utilize the DAP to enable specially-trained school nurse champions and IRTs to implement and sustain EB strategies to address the needs of LGBTQ high school students

#### Exploration phase

For the exploration phase, the DAP centers on recruiting, enrolling, and randomizing schools, followed by initial assessments of system, provider, and client data to identify school needs, strengths, barriers, and readiness to implement the EB strategies. Results of the initial assessments will be shared with the IC schools specifically via comprehensive summaries to be vetted by the IRTs and integrated into their respective planning for implementation.

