##### Qualitative data collection

Readiness interviews will consist of open-ended questions that will be asked of IC stakeholders at the system, provider, and client levels. These include 20 administrators, 20 school nurses, and 20 individuals randomly selected from the IRTs (*n* = 60). Interviews will explore if the necessary conditions exist for implementation and sustained use of the EB strategies and how best to optimize them. Questions will center on attitudes toward, access to, and availability of school and community supports for (a) suicide prevention, (b) LGBTQ youth, and (c) school nursing staff. Verbal and written information regarding school policies and practices pertinent to EB strategies will be collected. Specific questions will focus on transgender and intersex youth, i.e., perceptions and knowledge related to their risks for suicide, substance use, bullying, and truancy within school settings, and extant support. Finally, interviews will address pragmatic concerns (e.g., staffing and resources) and organizational factors (e.g., leadership and supportive culture/climate) [43, 47, 48, 62]. Results of these first assessments will inform IRT efforts to build implementation capacity and subsequent plans to implement and sustain EB strategies. For comparison purposes, a complementary set of interviews will be completed with the 20 nurses and the 20 administrators in the CC schools.

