##### Quantitative data collection

The 40 administrators and 40 school nurses in both the IC and CC schools will complete the first of an annual 30-min web-based survey that assesses organizational characteristics of schools and administrator/nurse work attitudes.

*Measures*. Demographics include age, gender, sexual orientation, race/ethnicity, education, employment, experience, geographical area of work, and activities performed in schools. Attitudes toward sexual and gender minorities will be assessed through two validated and reliable instruments, the *Attitudes Toward Lesbians and Gays Scale *[66] and the *Attitudes Toward Transgender Individuals Scale *[67]. Organizational culture and climate will be assessed via the *Organizational Social Context Scale*, which has good psychometric properties with Cronbach’s alphas ranging from 0.78 to 0.94 [42]. Climate includes three domains that affect use of EB strategies: (1) stress; (2) engagement; and (3) functionality. Culture includes (1) proficiency (responsiveness, competence) and (2) resistance (apathy, suppression). Work attitudes consist of two measures, *job satisfaction* (ten items) and *organizational commitment* (13 items), with good reliability and validity [68–70]. Attitudes toward adopting EB strategies will be assessed using the *Evidence-Based Practice Attitude Scale*, which examines: (1) intuitive appeal of EB practices; (2) likelihood of adopting if required; (3) openness; and (4) perceived divergence between EB practices and current practice [71]. Leadership will be measured via the *Multifactor Leadership Questionnaire (MLQ) *[72]. The MLQ assesses transformational leadership, transactional leadership, passive/avoidant leadership (laissez-faire), and perceived outcomes of leadership (extra effort, effectiveness, satisfaction). The MLQ has good psychometric properties with Cronbach’s alphas ranging from 0.76 to 0.90 [41, 69]. School-community linkages will be measured through an LGBTQ-specific modification of the *Collaborating with Community Subscale*, an eight-item tool based on the Measure of School, Family, and Community Partnerships [73]. This tool rates school partnership practices for integrating resources and services from the community to strengthen school programs, learning, and well-being for LGBTQ students on a scale of 1 (not occurring) to 5 (extensively occurring) and offers insight into improvement areas and future directions. An adapted *Assessment of *

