*Climate Embedding Mechanisms*
*(ACEM)* measure will elicit Likert scale ratings on how frequently each EB strategy is used, EB strategy adherence, and school leadership support [43]. In year 1, it will be completed by nurses and administrators to serve as a baseline assessment for each school.

*School administrative data*. Publicly-available administrative data will be used to assess faculty and staff retention, school truancy, graduation rates, drop-out rates, extracurricular student activities, and overall student characteristics, e.g., socioeconomic status and race/ethnicity, at participating schools.

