### Aim 2: conduct a cluster randomized controlled trial to assess whether LGB youth and peers in RLAS intervention schools report reduced suicidality, depression, substance use, and bullying, and increased safety compared to control schools

A cluster randomized controlled trial will assess whether LGBTQ students and their peers in RLAS intervention schools report reductions in suicidality, depression, substance use, bullying, and truancy related to safety concerns compared to those in usual care schools. Additional file 2 provides a study-specific checklist of information to include when reporting a cluster randomized trial. Additional file 3 contains a flow diagram of the phases of the randomized trial for the IC and CC schools. Randomization will take place in the exploration phase, as noted previously. Mahalanobis distance metric matching will be used to create pairs of similar schools [76], where one school in each pair will be randomly assigned to the IC.

The 2015 NM YRRS will offer baseline data for all schools and the 2017 and 2019 NM YRRS will yield follow-up data for the implementation and sustainment phases. From each school an average of 150 students complete the NM YRRS, for a sample size of 6000 per survey administration. Demographic data include gender, age, race/ethnicity, and sexual identity. Primary outcome measures assess suicide-related outcomes (“During the past 12 months, did you ever seriously consider attempting suicide?” “During the past 12 months, did you make a plan about how you would attempt suicide?” “During the past 12 months, how many times did you actually attempt suicide?”). Secondary measures assess depression (“During the past 12 months, did you ever feel so sad or hopeless almost every day for two weeks or more in a row that you stopped doing some usual activities?”), substance use (“During the past 30 days, on how many days did you have at least one drink of alcohol?” “During the past 30 days, how many times did you use marijuana?”), bullying (“During the past 12 months, have you ever been bullied on school property?”), and school safety (“During the past 30 days, on how many days did you not go to school because you felt you would be unsafe at school or on your way to or from school?”).

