### Aim 3: examine the individual, school, and community factors influencing implementation and outcomes

For the RLAS process evaluation, school health policies, practices, and community linkages, and the status of EB strategies will be assessed and compared across IC and CC groups. This will be done annually each spring via semi-structured interviews with all school administrators (*n* = 40) and nurses (*n* = 40) in years 1–4. To assess individual and school influences, the web-based surveys will be repeated with IC and CC groups each year. All qualitative interviews and surveys will follow the data collection and analysis procedures used in the preparation phase. Using these same qualitative analysis procedures, the content of coaching logs that describe in-depth implementation issues requiring technical assistance in the IC schools over the intervention period will also be assessed. Analysis of the web-based surveys aggregated across IC and CC schools will help identify and compare differences in the organizational characteristics of schools and administrator/nurse work attitudes over time.

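### The year-1 nurse and administrator survey that serves as baseline follows randomisation with no stated masking, which puts the survey and ACEM comparisons between arms over time at risk of bias

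*Protocol article*

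**What the plan says.** Under Aim 1, Exploration phase, the article gives the order of work as "recruiting, enrolling, and randomizing schools, followed by initial assessments of system, provider, and client data". Aim 2 repeats the timing: "Randomization will take place in the exploration phase, as noted previously".

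Under the same phase, Quantitative data collection states: "The 40 administrators and 40 school nurses in both the IC and CC schools will complete the first of an annual 30-min web-based survey". That survey holds the attitude, climate and culture, work-attitude and leadership scales and the adapted ACEM. Of the ACEM the article says: "In year 1, it will be completed by nurses and administrators to serve as a baseline assessment for each school".

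Two statements bear on who knows the allocation. Study design says: "Nurses in the IC will recruit IRT members (4–6 people) willing to work with them on implementing the six EB strategies". The readiness interviews of the exploration phase list their intervention-school participants thus: "These include 20 administrators, 20 school nurses, and 20 individuals randomly selected from the IRTs".

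The survey is repeated yearly. Under Aim 3 its analysis is to "identify and compare differences in the organizational characteristics of schools and administrator/nurse work attitudes over time", aggregated by arm. Aim 3, Data collection and analysis, also uses the ACEM to track strategy use in all 40 schools and names a need to assess diffusion to the controls.

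**The concern.** A baseline used to compare change between randomised arms should be measured before anyone can respond to the allocation. Here it comes after. The items are mostly subjective ratings from one nurse and one administrator per school.

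The survey also serves a different purpose in each arm. In intervention schools the answers become feedback reports that the team uses to find weak areas. Control schools receive no feedback until the final year. Intervention staff may therefore have a reason to report needs in year 1 and a different reason, after coaching and training, to report progress. An incentive that changes over time in one arm only is one that a change from baseline does not remove.

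At stake are the Aim 3 comparisons of organisational characteristics and work attitudes over time, and the reading of control-school drift. The article expects many schools to use some of the strategies already, so drift cannot be judged without a sound starting point.

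**Working it through.** **Sequence.**
1. Schools are enrolled and randomised, and initial assessments follow (Exploration phase). Aim 2 confirms the phase of randomisation.
2. The first staff survey is listed within that phase, with respondents already described by arm. Its ACEM part is named a baseline.
3. Implementation Resource Teams exist only in intervention schools, the intervention nurse recruits them, and their members are interviewed in the same phase. The intervention nurse therefore knows the allocation by about that time. For administrators and control staff this is an inference. The article does not say whether the survey precedes team formation.
4. Coaching starts in the preparation phase and training in the implementation phase. What could act on the year-1 answers is knowledge of allocation, not treatment.

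**Size.** The article gives no test, error rate or effect size for these surveys, so there is no figure to reproduce. The following is an illustration.

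- From the article: 20 schools per arm.
- Assumed: school-level SD of 1; correlation ρ between baseline and follow-up of 0.5 or 0.7; two-sided 5% level; normal approximation; independent arms (the matched pairs are ignored); no true effect; a shift of d SD in one arm at baseline only.

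For a change score, SE = √(2(1−ρ)) × √(2/20) and the bias has size d. With ρ = 0.5 the SE is 1 × 0.316 = 0.316. With ρ = 0.7 it is 0.775 × 0.316 = 0.245.

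For follow-up adjusted for baseline, SE = √(1−ρ²) × √(2/20) and the bias has size ρd. With ρ = 0.5 the SE is 0.866 × 0.316 = 0.274. With ρ = 0.7 it is 0.714 × 0.316 = 0.226.

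The false-positive rate is Φ(t − 1.96) + Φ(−t − 1.96), with t = bias/SE. For example, d = 0.2 and ρ = 0.5 in a change score give t = 0.632 and a rate of 0.097.

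| Baseline-only shift d | Change score, ρ 0.5 | Change score, ρ 0.7 | Adjusted, ρ 0.5 | Adjusted, ρ 0.7 |
|---|---|---|---|---|
| 0.1 SD | 6.2% | 6.9% | 5.4% | 6.1% |
| 0.2 SD | 9.7% | 12.9% | 6.5% | 9.5% |
| 0.3 SD | 15.8% | 23.2% | 8.5% | 15.3% |
| 0.5 SD | 35.3% | 53.2% | 15.0% | 34.1% |

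Two boundary cases complete the picture. A comparison of follow-up levels alone does not use the baseline, so a baseline-only shift biases it by 0. If the same shift d is present at baseline and at follow-up, the bias in the change score is d − d = 0.

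**The case against.** The strongest reply is that the article shows no planned test that this would spoil. The survey analysis under Aim 1 is descriptive and at school level, Aim 3 follows the same procedures, and no model includes the staff survey as a covariate. This stands. The percentages above describe a test that the article does not specify and cannot be read as error rates of the plan.

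Second, the article orders randomisation, not disclosure, and a condensed article may leave the moment of disclosure to the full protocol. This stands in part. Knowledge is well supported for intervention nurses and only probable for the others. But the order of randomisation and survey is stated, and it is not a gap that further detail would fill.

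Third, the same unblinded staff report every year. A constant reporting shift cancels under the present order, whereas with a clean baseline and unblinded follow-up it would enter the change in full. The arithmetic is right. Constancy, however, is an assumption, and the different use of the answers in the two arms gives no ground for it. It does show that moving the survey cures only the baseline.

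A reader might infer more than the documents support:

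- **That the baseline is shown to be contaminated.** The article establishes a sequence. Whether answers shifted, how far and in which direction is unknown.
- **That every Aim 3 comparison falls.** Yearly follow-up levels can be compared between arms without the baseline. The Stages of Implementation Completion scores and the team focus groups concern intervention schools only. Interviews and public administrative data supplement the ratings.
- **That the trial's main result is affected.** All five Aim 2 hypotheses use the student survey, with its 2015 round as baseline.

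**Conclusion.** The point holds as a risk of bias in a secondary aim. A survey called a baseline is taken after randomisation, from intervention nurses who may well know their arm and from other staff who probably may, and it is then used to compare arms over time and to judge diffusion to controls. The size and direction of any bias are unknown. Under the assumptions above, shifts of 0.2 to 0.5 SD confined to the baseline would give false-positive rates of about 10% to 35% in a change score at ρ = 0.5, and less with adjustment. The true figure could be close to 5% if there is little shift, or if the shift is constant and cancels. The change is worth making because it is cheap, not because harm has been shown.

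**What to change.** Have the nurse and the administrator of each school complete the year-1 web survey, ACEM included, after consent and before the allocation of their matched pair is disclosed. Nurse consent and administrator agreement are already conditions of eligibility, and nothing in the survey as described requires knowledge of the arm. The readiness interviews and the team-member interviews can stay after randomisation. The cost is a short delay in announcing allocation while 80 surveys (40 nurses and 40 administrators) come in. No measure is added. The article gives no timeline from which to state the length of the delay.

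If this is not possible, label the year-1 survey as post-randomisation and base between-arm inference on follow-up levels, adjusted for matched pair and for administrative data that predate randomisation.

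In either case, state in the protocol and in reports that follow-up ratings are unblinded self-report. Neither option removes that.
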